## Abstract

**Aims::**

Success of opening single (SOS)-comedy is a prospective multicenter study to compare the improvement in the decrease of myocardial viability by percutaneous coronary intervention (PCI) with that by optimal medical therapy (OMT) alone in patients with chronic total occlusion (CTO) of a single coronary artery.

**Methods and results::**

The risks and the benefits of both options (PCI and OMT) were listed in a CTO decision aid (DA). Eligible participants detected by invasive coronary angiography (ICA) or coronary computed tomography angiography (CCTA) were divided into PCI or OMT groups according to patients’ choice after shared-decision making process with DA. Participants will undergo positron emission tomography/computed tomography (PET/CT), cardiac magnetic resonance (CMR) and transthoracic echocardiography (TTE), and proceed to ICA and revascularization if possible. Blinded core laboratory interpretation will be performed for ICA, CCTA, PET/CT, CMR, and TTE. All participants will be followed up for 12 months. The primary endpoint is the improvement to the decrease of myocardial viability from baseline assessed with the use of PET/CT after 12-month follow-up.

**Conclusions::**

All of the patients are appropriately consented before enrolling in this study, which has been approved by the Ethics Committee. Results of SOS-COMEDY will be helpful to develop a strategy for single CTO patients.

## Introduction

1

A chronic total occlusion (CTO) is defined as a complete coronary arterial obstruction with Thrombolysis In Myocardial Infarction (TIMI) flow grade of 0 for longer than 3 months.^[1]^ CTOs have been identified in up to 20% of all patients referred for diagnostic angiography.^[2]^ However, the CTO procedural success rate is 60% to 70%, much lower compared with non-CTO percutaneous coronary intervention (PCI) success rate of 98%.^[2,3]^ In the past, patients with a CTO were often managed conservatively or surgically rather than with PCI.^[4]^ The barriers that only 8% to 15% of patients with CTO face during PCI-based revascularization are numerous^[5–7]^: lower expectation of procedural success; higher perceived risk of complications; increased technical complexity; motivation; and training or catheter lab resources.^[8]^ Due to improvements in technique and observational evidence that successful CTO intervention is associated with symptomatic relief of angina, lower rates of subsequent myocardial infarction (MI) and coronary artery bypass graft (CABG), and survival improvement,^[9–16]^ there is growing interest in percutaneous treatment of CTO. Not only European but also American guidelines have assigned a class IIa (level of evidence B) recommendation for CTO PCI. However, there is currently no consensus on which strategy is much better. As a result, we divided patients into different groups using decision aid (DA) instead of randomization to protect the interests of patients as well as to increase compliance.

It is well known that the amount of viable myocardium is the best indicator of long-term cardiac event-free survival after cardiac intervention.^[17]^ Most CTO registries do not report preprocedural ischemic burden or myocardial viability. As such, the benefits of successful CTO PCI may be underestimated by the inclusion of patients with no viability or little ischemia that could not be expected to benefit from a successful procedure.

There are several diagnostic approaches used in current clinical practice for assessment of myocardial viability. Analysis of wall thickness or myocardial contraction, and evaluation of cardiac perfusion or metabolism can be assessed using the following modalities: transthoracic echocardiography (TTE), cardiac molecular imaging techniques [positron emission tomography (PET), single photon emission computed tomography (SPECT)], cardiac magnetic resonance (CMR), or coronary computed tomography angiography (CCTA). The combined devices multislice computed tomography scanners with PET (PET/CT) are now widely used in clinical practice. This combination allows for wider morphologic assessments: coronary calcium scoring and noninvasive coronary angiography may be added to myocardial perfusion/metabolic imaging if necessary.

In practice, it is difficult to accurately assess the impact of PCI and/or optimal medical therapy (OMT) alone on clinical outcomes due to inclusion of patients with heterogeneous coronary artery disease such as multivessel disease. Thus, patients with CTO PCI of a single coronary artery are an optimal study population to compare the relatively absolute impacts of PCI and OMT on clinical outcomes. Therefore, the aim of this study was to compare the improvement in the decrease of myocardial viability by PCI with that by OMT alone in patients with CTO of a single coronary artery in the drug-eluting stent (DES) era.

## Methods

2

### Design

2.1

To evaluate the change of myocardial viability in single CTO patients with successful PCI or with only OMT, we propose to conduct a prospective, nonrandomized multicenter trial using with a DA. The Ethics Committee in The First Affiliated Hospital of Dalian Medical University approved all study procedures. Patients and interventional cardiologists for this trial are to be recruited at 4 hospitals. All cardiologists have more than 10 years of PCI experience and perform CTO cases at least 50 cases each year.

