### Participants

2.2

Patients who satisfy all the inclusion criteria will be enrolled. Patients who meet any of the exclusion criteria will not be enrolled. The patients will give written informed consent to undergo PET/CT, CMR and TTE at baseline and at the 12-month follow-up, and participants will subsequently precede to invasive coronary angiography (ICA) and revascularization within 2 days of noninvasive tests (Fig. 1). Blinded core laboratory interpretation will be performed for ICA, CCTA, PET/CT, CMR, and TTE.

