## Study definitions

4

A CTO was defined as a complete occlusion with TIMI flow grade 0 antegrade through the affected segment of >3 months’ duration in the opinion of the operator based on clinical features, angiographic features, and/or previous imaging. Procedural success was defined as < 50% residual stenosis with TIMI flow grade 3 antegrade. Failure was defined as failure to cross the occlusion or reduce obstruction to less than 50% in the target CTO.

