### Treatment details

4.2

At baseline, 3 months, 6 months, and 12 months recommendations for therapy are made to the physicians in line with guideline.^[18]^ The goal of antihypertensive therapy is to achieve a blood pressure of less than 140/80 mm Hg. The aim of antilipid therapy is to achieve levels of low-density lipoprotein (LDL) < 1.8 mmol/L. In the first instance, statin therapy will be initiated and then increased with the addition of a second agent if necessary. For patients with a BMI of > 25 kg/m^2^, the physicians are asked to refer the patient for dietary advice. Similarly, smokers are referred to the smoking cessation clinic. In the case of diabetics with raised blood sugar, the physicians are asked to measure HbA1c and to ensure that the patients’ subsequent therapy is tailored to achieve an HbA1c of less than 6.5 mg/dL. OMT included antiplatelet medication, β-blockers, rennin angiotensin system blockers, nitrates, calcium channel blockers, and aggressive lipid lowering therapy. The decision to pursue invasive treatment as well as site of access, type of stents, use of intravascular ultrasound, and use of glycoprotein IIb/IIIa receptor inhibitors was left to the discretion of the physician. Prior to PCI, all patients were pretreated with loading doses of aspirin (300 mg) and clopidogrel (300–600 mg) unless they were previously medicated with these antiplatelet agents. PCI was performed using contemporary techniques such as bilateral injections, specialized stiff hydrophilic wire with a tapered tip, and microcatheters in a retrograde approach, when available. All interventions and procedural anticoagulations were performed in accordance with current standard guidelines.^[19]^

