
## Conclusions

10

This study will be the first multicenter study to evaluate the effect of PCI and/or OMT on myocardial viability in patients with single-vessel CTO using combined PET/CT during long-term follow-up. The patients were divided after shared decision making process, which can protect the interests of patients as well as increase compliance. Furthermore, the study will show the effects of PCI and/or OMT strategies on the clinical outcomes in patients with CTO of a single coronary artery. Thus, SOS comedy will indicate the optimal treatment modality for single lesions resulting in CTO.

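### The Design section compares successful PCI with OMT, while other sections form the groups by choice; followed literally, it would select the PCI arm on a post-procedure result

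*Protocol article*

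**What the plan says.** The protocol article describes the groups in several ways.

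- **Section 2.1, Design.** The object of study is viability change in "single CTO patients with successful PCI or with only OMT".
- **Abstract, Methods and results.** Eligible participants "were divided into PCI or OMT groups according to patients’ choice after shared-decision making process with DA". Section 10, Conclusions, agrees: "The patients were divided after shared decision making process".
- **Section 1, Introduction.** The closing aim sets PCI against OMT alone and attaches no success condition.
- **Section 4.2, Treatment details.** "The decision to pursue invasive treatment as well as site of access, type of stents" and other procedural matters are left to the physician.
- **Section 2.2, Participants.** After the imaging, "participants will subsequently precede to invasive coronary angiography (ICA) and revascularization within 2 days of noninvasive tests", with no restriction to one group. The parallel sentence in the Abstract adds a feasibility condition.

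Section 4, Study definitions, requires both residual stenosis below 50% and TIMI grade 3 flow for procedural success. "Failure was defined as failure to cross the occlusion or reduce obstruction to less than 50% in the target CTO". Neither definition says in which group a failed procedure is analysed. Section 8 compares groups and treatment strategies without choosing among these descriptions.

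**The concern.** A patient's choice is fixed before the procedure. Procedural success is observed afterwards and plausibly depends on lesion and patient characteristics that may also bear on recovery of viability. Restricting the PCI group to successes would remove the lesions that could not be opened from one arm only. The equivalent lesions in the OMT group are never attempted, so they stay in.

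Such a contrast would no longer answer the question the decision aid puts to the patient, which is which strategy to choose before anyone knows whether the vessel will open. If lesions that open also respond better, the contrast favours PCI even when PCI does nothing. Section 10 expects the study to indicate the best treatment modality, and a success-only contrast would not support that.

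The point goes beyond detail left to an analysis plan. Any analysis plan would have to depart either from section 2.1 or from the Abstract and Conclusions.

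**Working it through.** **1. The descriptions side by side**

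| Place | What puts a patient in the PCI group | When it is known |
|---|---|---|
| Section 2.1 | PCI succeeded | after the procedure |
| Abstract; section 10 | choice after the decision aid | before |
| Section 1 (aim) | PCI, no success condition | not specified |
| Section 4.2 | physician decides on invasive treatment | before |

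A patient who chooses PCI and has a failed procedure belongs to the PCI group under the Abstract and is outside it under section 2.1.

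**2. How many patients this could touch**

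Section 1 cites a background CTO success rate of 60–70%, so failure is 100 − 70 = 30% to 100 − 60 = 40%. This is not a design assumption. Section 2.1 requires operators with more than 10 years of PCI experience and at least 50 CTO cases a year, and the trial's own failure rate is not stated. I therefore use f = 10% to 40%.

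**3. Size of the bias if failures were dropped and PCI had no effect**

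Inputs:
- 200 patients less 15% drop-out (section 7) = 170. An equal split is assumed, giving 85 per chosen strategy.
- Both chosen groups are assumed to contain the same mix of lesions.
- Response is p_s in lesions that would open and p_f in those that would not. Both are assumptions; the article gives neither.

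Formulas:
- True rate in both groups: m = (1 − f)·p_s + f·p_f
- False benefit when failures are dropped: p_s − m = f·(p_s − p_f)
- Rejection: two-sided test of two proportions at α = 0.05, pooled variance under the null, both tails counted, with 85·(1 − f) patients left in the PCI group and 85 in OMT

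Example, f = 0.30, p_s = 0.50, p_f = 0.20: m = 0.7 × 0.50 + 0.3 × 0.20 = 0.41; false benefit = 0.3 × 0.30 = 0.09; 59.5 v 85 patients; rejection 18.8%.

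| Assumed p_s v p_f | f | m | False benefit | Rejection (nominal 5%) |
|---|---|---|---|---|
| equal | any | – | 0 | 5% |
| 40% v 30% | 10% | 39% | 1 point | 5.2% |
| 40% v 30% | 30% | 37% | 3 points | 6.6% |
| 40% v 30% | 40% | 36% | 4 points | 7.6% |
| 50% v 20% | 10% | 47% | 3 points | 6.7% |
| 50% v 20% | 15% | 45.5% | 4.5 points | 8.7% |
| 50% v 20% | 30% | 41% | 9 points | 18.8% |
| 50% v 20% | 40% | 38% | 12 points | 27.8% |

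If failures were instead counted as OMT, the false benefit would be 2f·(p_s − p_f)/(1 + f). At 50% v 20% this is 0.6 × 0.30/1.3 = 13.8 points for f = 30% and 0.8 × 0.30/1.4 = 17.1 points for f = 40%, with rejection of 42% and 56%. No section describes such a reassignment.

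**4. What analysis by chosen strategy costs in power**

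Section 7 gives 80% improvement for PCI and 20% for OMT, at different improvement thresholds. Assume 80% applies to successes and 20% to failures and OMT:
- 60% success: 0.6 × 0.80 + 0.4 × 0.20 = 0.56
- 70% success: 0.7 × 0.80 + 0.3 × 0.20 = 0.62

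Against 20%, the difference falls from 60 points to 36 or 42. Power at 85 per group is 99.9% or more in both cases.

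**5. The gap between success and failure**

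Residual stenosis below 50% with TIMI flow below 3 does not meet the success definition. Nor does it meet the failure definition, because the lesion was crossed and the obstruction reduced. The outcome is neither.

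**The case against.** The strongest reply is that the exclusion is inferred. The reference to successful PCI stands in an objective clause, not in an allocation or analysis rule. The allocation sentences use choice, the Introduction's aim has no success condition, and section 8 speaks of treatment strategies. Most of the article already points to the grouping recommended here. The flow diagram is not shown, and analysis sets are commonly left to the full protocol or analysis plan. All of this stands. A reader might infer that failed PCI will be dropped or moved to OMT, or that 30–40 of every 100 PCI patients will be lost. The article says neither.

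On size, the 60–70% is a cited background rate, and patients unsuitable for PCI are excluded, so the trial's failure rate may be lower. The 50% v 20% case is only one possibility, and the 38–47% null rate it implies is about twice the 20% that section 7 gives for OMT. Section 7 also states its 80% for PCI, not for successes, and its 20% for OMT, not for failed PCI. These limits stand too, which is why the bias is given as a range from zero.

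Section 2.2 may simply be loosely condensed, and the gap in the success and failure definitions leaves a patient without a group only if success defines the group.

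The objection does not remove the conflict itself: section 2.1 and the Abstract describe different populations in the current text.

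**Conclusion.** The inconsistency is real and should be fixed; confidence is moderate. If section 2.1 governed the analysis, the PCI arm would be conditioned on a post-procedure result with no counterpart under OMT, and the comparison would lean toward PCI whenever lesions that open also respond better.

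The documents do not fix the size. With failure rates of 10–40%, dropping failures gives a false benefit of zero with no response gap, 1–4 points (about 5–8% rejection) at 40% v 30%, and 3–12 points (7–28%) at 50% v 20%. These figures assume no PCI effect, 85 per chosen strategy, the same lesion mix in both groups, and response rates that are mine. Counting failures as OMT would give more.

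The stronger reading, that the primary analysis as planned is best-case PCI against all OMT, is not supported: most of the text groups by choice.

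**What to change.** 1. Define the primary comparison by the strategy recorded at the end of the decision-aid discussion. Keep failed PCI in the PCI group and crossovers in the group they chose. Change section 2.1 to match and say so in section 8.
2. Make successful PCI versus OMT a labelled secondary analysis. For it, count every attempted PCI that does not meet the section 4 success definition as not successful, which closes the gap for TIMI flow below 3.
3. Record chosen and received strategy separately.
4. Reconcile the Abstract, section 2.2 and section 4.2 on who decides and which participants go to revascularization.

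The cost is mainly wording in sections 2.1, 2.2, 4, 4.2 and 8. Section 3 reports 240 patients already enrolled, so the chosen strategy must be retrieved for them if it was not recorded separately. The estimated PCI effect will be smaller than in a success-only analysis, with power still above 99% under the assumptions shown. The change does not remove confounding: groups formed by choice in a nonrandomized study can still differ in prognosis.

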### Participants

2.2

Patients who satisfy all the inclusion criteria will be enrolled. Patients who meet any of the exclusion criteria will not be enrolled. The patients will give written informed consent to undergo PET/CT, CMR and TTE at baseline and at the 12-month follow-up, and participants will subsequently precede to invasive coronary angiography (ICA) and revascularization within 2 days of noninvasive tests (Fig. 1). Blinded core laboratory interpretation will be performed for ICA, CCTA, PET/CT, CMR, and TTE.

**Figure 1 F1:**
[figure not shown]
Study flow diagram outlining the study design.

### Inclusion criteria

2.3

Eligible patients include age 18 to 80, with a history of stable or unstable angina pectoris based on standard definitions for angina pectoris used in previous trials, whose left ventricular ejection fraction (LVEF) > 35% on TTE measurement, who is found single lesion occluding the coronary artery, who is with or without stenosis of other coronary arteries (≤ 50% diameter stenosis) detected by previous ICA or CCTA, who have a follow-up appointment with their clinician, and who are available for a clinic follow-up 12 months after enrollment.

#### Exclusion criteria

2.3.1

The trial will exclude patients who have an acute Q-wave MI within the last 3 months, who have undergone revascularization in the nonculprit artery during the latest month, who are unsuitable for PCI, who are unable to tolerate dual antiplatelet treatment (DAPT), who have severe abnormal hematopoietic system (such as platelet count of < 100×10^9^/L or > 700×10^9^/L and white blood cell count of < 3×10^9^/L), who have active bleeding or bleeding tendency, who have severe coexisting conditions (such as severe renal insufficiency (GFR < 60 mL/min × 1.73 m^2^), severe hepatic dysfunction [elevated alanine transaminase (glutamic-pyruvic transaminase) or aspartate aminotransferase (glutamic-oxal acetic transaminase) level by more than 3-fold of the normal limitation], acute or chronic heart failure (NYHA III-IV), acute infectious diseases, immune disorders, malignancy), who have asthma, who have life expectancy < 12 months, who are pregnant or are planning pregnancy, who have drug allergies or contraindications to aspirin, clopidogrel, ticagrelor, statins, radiocontrast, anticoagulants, or stents, who are participating or planning to participate in another clinical trial during the same period, who have major learning barriers such as visual or hearing impairment or dementia that would compromise their ability to give written informed consent or use the decision aid.

## Interventions

3

This study will be conducted in accordance with the Declaration of Helsinki and with the approval of the ethical committees of the 4 participating institutions. Recruitment commenced on October 20, 2015, and as of November 2017, 240 patients have been enrolled. The trial is registered under www.clinicaltrials.gov: NCT02767401.

## Study definitions

4

A CTO was defined as a complete occlusion with TIMI flow grade 0 antegrade through the affected segment of >3 months’ duration in the opinion of the operator based on clinical features, angiographic features, and/or previous imaging. Procedural success was defined as < 50% residual stenosis with TIMI flow grade 3 antegrade. Failure was defined as failure to cross the occlusion or reduce obstruction to less than 50% in the target CTO.

### Decision aid (DA)

4.1

As shown in Fig. 2, in the pilot trial of DA, the major benefits and risks for patients using both strategies are listed. Only options with the most concerns will be presented in the final version of the questionnaire, including outcomes, complications, costs, follow-up requirement, further revisualization, contrast-induced nephropathy, and radiation injury. With the DA, the clinicians introduce all major benefits and risks if CTO patients choose PCI or medication using the words such as “during the next 5 years, among 100 patients like you, 5 patients have a risk of myocardial infarction…”.

**Figure 2 F2:**
[figure not shown]
The pilot study of decision aid (DA) of SOS-comedy for patients with CTO lesions both in English (A) and Chinese (B) version. CTO = chronic total occlusion, SOS = success of opening single.

### Treatment details

4.2

At baseline, 3 months, 6 months, and 12 months recommendations for therapy are made to the physicians in line with guideline.^[18]^ The goal of antihypertensive therapy is to achieve a blood pressure of less than 140/80 mm Hg. The aim of antilipid therapy is to achieve levels of low-density lipoprotein (LDL) < 1.8 mmol/L. In the first instance, statin therapy will be initiated and then increased with the addition of a second agent if necessary. For patients with a BMI of > 25 kg/m^2^, the physicians are asked to refer the patient for dietary advice. Similarly, smokers are referred to the smoking cessation clinic. In the case of diabetics with raised blood sugar, the physicians are asked to measure HbA1c and to ensure that the patients’ subsequent therapy is tailored to achieve an HbA1c of less than 6.5 mg/dL. OMT included antiplatelet medication, β-blockers, rennin angiotensin system blockers, nitrates, calcium channel blockers, and aggressive lipid lowering therapy. The decision to pursue invasive treatment as well as site of access, type of stents, use of intravascular ultrasound, and use of glycoprotein IIb/IIIa receptor inhibitors was left to the discretion of the physician. Prior to PCI, all patients were pretreated with loading doses of aspirin (300 mg) and clopidogrel (300–600 mg) unless they were previously medicated with these antiplatelet agents. PCI was performed using contemporary techniques such as bilateral injections, specialized stiff hydrophilic wire with a tapered tip, and microcatheters in a retrograde approach, when available. All interventions and procedural anticoagulations were performed in accordance with current standard guidelines.^[19]^

